## Inclusion criteria

To be eligible for inclusion in the study, subjects must fulfil all the following criteria:

1. Willing and able to give written informed consent for participation in the study.
2. Clinical diagnosis of Amyotrophic Lateral Sclerosis (ALS).
3. Male or female patients between 18 to 80 years (inclusive).
4. Forced Vital Capacity (FVC) ≥ 65% of predicted value for gender, height and age at screening.
5. Evaluated with ALSFRS-R and Norris clinical rating scales for at least the past 4 weeks before study drug administration.

## Exclusion criteria

Subjects must not enter the study if any of the following exclusion criteria are fulfilled:

1. Unable to understand information about the study or are expected not to collaborate with the study team.
2. Concurrent serious disease, other than ALS, at the discretion of the Investigator.
3. Pregnancy.
4. Patients of childbearing potential not willing to use adequate double contraception^[[1]](#footnote-2)^ with < 1% failure rate after the screening visit until the last visit.
5. Addiction to drugs or alcohol.
6. Confirmed HIV, hepatitis B or hepatitis C.
7. Known bleeding disorders or abnormal bleeding events.
8. Treatment with anticoagulant drugs warfarin and novel oral anticoagulants (NOAC) within the last 14 days prior to screening.
9. Treatment with Riluzole or Lamotrigine within the last 28 days prior to study drug administration.
10. Hypersensitivity to dextran sulfate.
11. Poor venous access.
12. Patients with clinically significant abnormal PK-INR, fibrinogen, von Willebrand factor and activated partial thromboplastin time (APTT) at screening.

## Prior and concomitant therapy

Patients must not use anticoagulant drugs warfarin and novel oral anticoagulants (NOAC) during the study, and within the last 14 days prior to screening. Patients must not use Riluzole or Lamotrigine during the study, or within the last 28 days prior to study drug administration. Chronic intake of medication including herbal remedies and over the counter drugs on a stable dose for more than two months before screening is allowed. Hormonal contraception is allowed. If there is a need for use of other medication due to intercurrent disease at any time during the study period until end of study the decision will be declared by the patient to the investigator.

## Withdrawal of patients from therapy or assessment

### General withdrawal criteria

Subjects are free to discontinue their participation in the study at any time. Biological samples from the subject will be disposed of, if not already analysed and documented.

Subjects may be discontinued from the study at any time at the discretion of the Investigator for any of the following reasons:

- Severe non-compliance to study protocol procedures
- Significant AEs posing a risk for the subject, including risks of grade B (as stated in Appendix 1).
- Patient contracts a serious disease or has an accident

### Criteria for temporary withdrawal

A subject will be temporarily withdrawn from the study for the following reason:

- Decrease of platelet or neutrophil counts below 50 % of the level at inclusion, until recovery of laboratory findings.

### Criteria for permanent withdrawal

A subject will be permanently withdrawn from the study for the following reasons:

- Withdrawal of informed consent
- in case of pregnancy, planned pregnancy or non-compliance with set requirements for contraception
- if treatment with anticoagulants warfarin/NOAC is necessary
- concomitant treatment with Riluzole or Lamotrigine

### in case of Serious Adverse Events (SAE) that are assessed as possibly or probably related to study treatment, including all risks categorized as of grade C (as stated in Appendix 1).

### Procedures for discontinuation of a subject from the study

A subject who prematurely discontinues participation in the study will always be asked about the reason(s) for discontinuation and the presence of any AEs. If possible, the patient will be seen by the investigator and assessed according to the procedures scheduled for the End-of-study follow-up (Visit 9). Any ongoing AE will if possible be followed as described in ‘Section 12.3.6’

In the event that a patient or their partner becomes pregnant in the period between Visit 2 and Visit 9, the outcome of the pregnancy should if possible be followed.

The reason and date the subject is removed from the study is to be documented in the Case Report Form (CRF) and in their medical records.

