| **Safety and efficacy assessments**  Safety:   - AE assessments will start at administration of the first dose of ILB. - Physical exam will be obtained at all visits. On the days of ILB administration (Visit 2 to Visit 6), physical examination will be obtained before dosing. - Vital signs (blood pressure, heart rate and body temperature) will be obtained at all visits. - 12-lead ECG will be obtained at Visit 1 and Visit 7. - Lab tests (clinical chemistry, haematology, haemostatis) will be obtained at all visits. On the days of ILB administration (Visit 2 to Visit 6), lab tests will be obtained before dosing.   Efficacy:   - The investigator will complete the ALS Functional Rating Scale - Revised (ALSFRS-R) at all visits. On the days of ILB administration, rating scales will be completed before dosing. - The investigator will complete the Norris functional rating scales at all visits. On the days of ILB administration, rating scales will be completed before dosing. - Blood and cerebrospinal fluid (CSF) samples for evaluation of the ALS biomarker Neurofilament Light chain (NFL) will be obtained at Visit 1 after eligibility is confirmed and at Visit 7. - Blood and CSF samples for analysis of biomarkers for neurological disorders (see 11.4.2) will be obtained at Visit 1 after eligibility is confirmed and at Visit 7. - Respiratory function (FVC) will be evaluated at all visits. On the days of ILB administration (Visit 2 to Visit 6), respiratory function will be assessed before dosing. - Quality of Life (QoL) will be evaluated using Visual Analogue Scale (VAS)-based questionnaire filled out by patient and, if applicable, a next of kin, at Visit 1, Visit 2, Visit 4, Visit 6 and Visit 8. - Autonomous symptoms will be evaluated according to a 4-grade scale for a range of parameters at all visits. - Levels of Hepatocyte Growth Factor (HGF), pharmacokinetic measurements and effect APTT will be obtained in conjunction with the first and last ILB administration (Visit 2 and Visit 6). Blood samples will be obtained pre-dose, 30 minutes and 1, 2, 2.5, 3, 4, 6 hours after dosing. | |

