### Primary endpoint

- Frequency, seriousness and intensity of Treatment-emergent Adverse Events (TEAEs)
- Physical examination
- Vital signs
- Electrocardiogram (ECG) recordings
- Safety laboratory measurements: clinical chemistry, haematology including activated partial thromboplastin time (APTT)

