## Overall study procedures

Subjects will be screened for eligibility according to pre-defined criteria (see section 9.3 and 9.4) within 30 days prior to first administration of IMP (Visit 1a; day -30 to -7). If eligibility is confirmed at Visit 1a, the patients will return at Visit 1b (day -23 to -1) for collection of CSF and blood for analysis of NFL and other biomarkers of neurological disorders (see 11.4.2), and – if consented by patient – exploratory purposes (see 11.5). If it is found to be appropriate by patient or Investigator, the screening tests can be performed over several visits to avoid too strenuous strain on patient and next of kin.

Each subject will receive oral and written information about the study and the planned investigations and will have to give his or her signed and dated informed consent before any study-related procedures are initiated. On recruitment to the study, the patients will be evaluated for inclusion and exclusion criteria, and undergo a baseline assessment to include demographics, medical history, concomitant medication, vital signs, physical examination (including weight and height), ECG, haematology, and clinical chemistry. Patients will also complete a baseline assessment on the ALS Functional Rating Scale (ALSFRS-R), Norris rating scale and a quality of life assessment (Appendix 2-5). The patients will during 5 visits be administered ILB 1 mg/kg per week (Visit 2 to Visit 6), followed by 3 follow up visits (Visit 7 to Visit 9) over 10 weeks after the last dose. During the clinical trial, the patients will undergo regular assessments for safety and efficacy parameters.

The overall schedule of events for the study is presented in Table 2. For the visits with critical time points for study assessments, detailed schedule of events are presented in Table 3 (Visit 2 and Visit 6) and Table 4 (Visit 4). The procedures for all study assessments are described in detail in section 11.

Table 2 Schedule of events

| **Visit** | **1a** | **1b** | **2** | **3** | **4** | **5** | **6** | **7** | **8** | **9** |
| --- | --- | --- | --- | --- | --- | --- | --- | --- | --- | --- |
|  | Screening | Screening | Dosing^7^ | Dosing^7^ | Dosing^7^ | Dosing^7^ | Dosing^7^ | Follow-up | Follow-up | End of study  follow-up |
| **Day** | -30 to -7 | -23 to -1 | 1 | 8 | 15 | 22 | 29 | 36 | 50 | 99 |
| **Time window (days)** |  |  |  | ± 3 | ± 3 | ± 3 | ± 3 | ± 3 | ± 7 | ± 7 |
| Informed consent | X |  |  |  |  |  |  |  |  |  |

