9.6.5 Subject replacement

A subject that has not received any IMP treatment will be replaced. Subjects who are prematurely withdrawn from the study for any reason except the occurrence of AEs assessed as possibly or probably related to study treatment may be replaced during the course of the study.

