### ECG

All ECG data will be listed for each subject and summarised as the vital signs parameters including absolute and percent change since baseline using summary statistics. In addition, ECGs will be categorised as: “normal, abnormal, not clinically significant”, or “abnormal, clinically significant” (as judged by the Investigator) and summarised by visit.

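### A dosed patient who leaves the study before Visit 7 has no protocol-scheduled post-dose ECG, because the early-discontinuation visit follows the Visit 9 list, which has none

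*Protocol*

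**What the plan says.** Section 7.1.1 lists "Electrocardiogram (ECG) recordings" among five primary safety items. The others are treatment-emergent adverse events, physical examination, vital signs and safety laboratory tests.

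The synopsis fixes the timing: "12-lead ECG will be obtained at Visit 1 and Visit 7". Table 2 agrees, marking ECG at Visits 1a and 7 and at no other visit. The detailed schedules for Visits 2, 4 and 6 (Tables 3 and 4) have no ECG row.

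Under Section 16.5.3, ECG data are listed per patient and "summarised as the vital signs parameters including absolute and percent change since baseline using summary statistics". They are also classed by the investigator for clinical significance, by visit. Section 16.7.2 uses observed data only.

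For a patient who leaves the study early, Section 9.6.4 provides for an examination, where possible, "assessed according to the procedures scheduled for the End-of-study follow-up (Visit 9").

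Two routes out of the study are safety-related. Section 9.6.1 allows discontinuation for "Significant AEs posing a risk for the subject, including risks of grade B (as stated in Appendix 1"). The permanent-withdrawal criteria that end just before Section 9.6.4 include withdrawal "in case of Serious Adverse Events (SAE) that are assessed as possibly or probably related to study treatment". Section 9.6.5 says that patients withdrawn "for any reason except the occurrence of AEs assessed as possibly or probably related to study treatment may be replaced".

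**The concern.** Each patient has one scheduled post-dose ECG, and it falls after all five doses. Someone withdrawn during the dosing weeks leaves before it, and the exit assessment is modelled on a visit that has no ECG. Such a patient can comply fully with the protocol and still have no tracing to compare with baseline.

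This loss is related to outcome. Appendix 1 uses low pulse and low systolic pressure to define grades B and C of allergic reaction, and both grades are named in the discontinuation or withdrawal criteria. The autonomic symptom form (Appendix 6), which is on the Visit 9 list, asks about palpitations and irregular heart rhythm. The exit visit thus asks about rhythm symptoms without requiring a recording. At stake is whether the post-dose ECG summary includes the patients in whom a change would be most informative.

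**Working it through.** The protocol gives no figure to reproduce on this point. The check sets the schedule beside the discontinuation rule.

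**Step 1: when ECG is scheduled.** The day row of Table 2 reads "Day | -30 to -7 | -23 to -1 | 1 | 8 | 15 | 22 | 29 | 36 | 50 | 99", for Visits 1a, 1b and 2 to 9 in order. Matching the ECG row to this header cell by cell gives marks at Visit 1a (day -30 to -7) and Visit 7 (day 36) only. The Visit 9 cell (day 99) is blank.

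**Step 2: position relative to dosing.** Doses fall on days 1, 8, 15, 22 and 29. Visit 7 is nominally 36 - 29 = 7 days after the last dose.

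**Step 3: what the exit visit contains.** The Visit 9 column of Table 2 holds concomitant medication, physical examination, vital signs, FVC, haematology, clinical chemistry, pregnancy test, ALSFRS-R and Norris, autonomic symptoms and adverse events. Of the five primary items, four are covered and ECG is not.

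**Step 4: scheduled post-dose ECGs per dosed patient.**

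- Attends Visit 7: 1.
- Leaves the study before Visit 7 and attends the discontinuation visit: 0.
- Leaves the study before Visit 7 and does not attend: 0.

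The second line is the avoidable one.

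**Step 5: who can be replaced.** Leavers for other reasons may be replaced, and their replacements can supply a Visit 7 ECG. Leavers with possibly or probably related adverse events fall outside that provision.

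**Step 6: scale, by assumption only.** No dropout rate is stated. Suppose k of the 15 planned patients leave before Visit 7 and are not replaced, and no ECG abnormality is seen in the remaining n = 15 - k. The exact two-sided 95% upper limit on the true rate is 1 - 0.025^(1/n):

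| k (assumed) | n | Upper limit |
| --- | --- | --- |
| 0 | 15 | 21.8% |
| 1 | 14 | 23.2% |
| 2 | 13 | 24.7% |
| 3 | 12 | 26.5% |
| 5 | 10 | 30.8% |

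The loss of precision is modest. These limits also treat the n patients as representative of all who were dosed, which is doubtful if the absentees left because of related adverse events. The concern is therefore who is missing, more than how many.

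**The case against.** Much of the opposing case stands, and it limits the point in four ways.

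- **A reader might infer that early leavers have no post-dose ECG at all.** The documents do not support that. Section 12.3.6 has adverse events treated according to clinical practice, the opening of Section 11 permits repeat tests for abnormal results, and Section 16.5.3 lists all ECG data, which would include an unscheduled tracing. A patient with palpitations is a likely candidate for one. What the documents show is that none is required.
- **A reader might infer that anyone who stops dosing early is affected.** Section 9.6.4 concerns leaving the study. A patient who misses doses but stays in follow-up still has Visit 7. The dividing line is attendance at Visit 7, not tolerance of treatment.
- **A reader might infer a definite share of lost data, such as 7% to 20% from one to three leavers out of 15.** That rests on an assumed dropout and ignores replacement, which can restore the count and can take the number dosed above 15.
- **The effect on the primary objective is partial.** Four of the five items are on the Visit 9 list, the physical examination includes a cardiac assessment, and the analysis is descriptive with no decision rule on ECG.

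None of this closes the gap. An optional ECG is recorded selectively, and a statistical analysis plan cannot analyse a recording that was never made.

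**Conclusion.** The point holds in a limited form. Followed as written, the protocol gives no scheduled post-dose ECG to a dosed patient who leaves the study before Visit 7, even one who attends the discontinuation visit. The scheduled post-dose ECG summary would describe only patients who attended Visit 7. The omission is selective, because patients withdrawn for possibly or probably related adverse events are among those affected and fall outside the replacement provision.

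Its size cannot be derived from the document, and it is nil if nobody leaves before Visit 7. It touches one of five descriptive primary items. It is worth correcting because the missing tracings would come from the patients of most interest for safety and the correction is cheap. The conclusion rests on the agreement of Table 2 and the synopsis on ECG timing, and on reading Section 9.6.4 as limiting the exit assessment to the Visit 9 procedures.

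**What to change.** - **Section 9.6.4:** state that a dosed patient who leaves the study before Visit 7 has the Visit 9 assessments plus the 12-lead ECG otherwise due at Visit 7. Patients who leave after Visit 7 keep the Visit 9 list unchanged.
- **Section 16.5.3:** present that ECG in a separate early-discontinuation row, with change from baseline, investigator category and days since last dose. Count it in a tally of patients with any clinically significant abnormality after dosing. Do not pool it with Visit 7, because it may follow any of doses 1 to 5 at a variable interval, whereas the Visit 7 ECG is nominally 7 days after the fifth.

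The cost is one standard, non-invasive recording at a visit already arranged, one added sentence and a CRF page. The drawback is the variable timing of the exit ECG, which the separate row makes visible. No dose, stopping rule or treatment changes.

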9.6.5 Subject replacement

A subject that has not received any IMP treatment will be replaced. Subjects who are prematurely withdrawn from the study for any reason except the occurrence of AEs assessed as possibly or probably related to study treatment may be replaced during the course of the study.

# TREATMENT

## Treatment administration

The investigational medicinal product ILB will be given 1 mg/kg as single short-term s.c. injections in the abdomen, the thigh or the buttock, in that order of priority. The maximum volume to be injected at each injection site is approximately 2 ml and the number of injections per subject may range between 1 and 3 sites depending on the volume to be injected. Each administration should occur within ±3 days from the day specified in Table 2, with at least 4 days between two IMP administrations. After all other visit-specific assessments are completed (Table 2), ILB administration will be performed by the staff at the study site, and the subjects will be observed for at least 3 hours after injection.

## Identity of Investigational Medicinal Product

The IMP contains 20 mg/ml ILB and 9 mg/ml NaCl and is a sterile, colourless to pale yellow solution for subcutaneous injection. The active pharmaceutical ingredient is a type of low molecular weight dextran sulfate (LMW-DS, approx. 20 % sulfate, Mw 5 kDa).

## Packaging and labelling

The IMP (ILB 20 mg/ml) is filled in a 10 ml glass vial sealed with a rubber stopper and a tear-off aluminium cap. The vials will be provided in paper boxes and there will be 10 x 10 ml glass vials in each box. Each vial will be labelled with the information in Figure 2, and each paper box will be labelled with the information in

Figure 3.

Labelling and distribution of ILB to the trial site is done in accordance with local law, trial requirements and Good Clinical Practice.

Figure 2 Information on IMP vial label

[figure not shown]

Figure 3 Information on IMP box label

[figure not shown]

## Conditions for storage

The IMP must be stored at +2°C to +8°C and should not be kept at room temperature for more than one hour prior to dosing.

## Dispensing and accountability

The investigator will maintain a drug dispensing log detailing the dates and quantities of IMP received, dispensed and used by each subject, and study medication returned at the end of the study. Any discrepancies between dispensed and returned IMP must be explained and documented. Unused, partially used and empty ILB vials are to be sent to the Sponsor.

## Treatment compliance

The IMP will be administered at the research clinic under medical supervision to ensure compliance.

# STUDY ASSESSMENTS

The procedures and timing of the study assessments are described in the sections below. For overview, see also the schedule of events in Table 2.

For visits with critical time points for blood sampling, detailed schedule of events are presented in Table 3 (Visit 2 and Visit 6) and Table 4 (Visit 4).

In case of deviations from normal, repeated tests can be performed.

## Recording of data and time windows

The Principal Investigator will provide the Sponsor with all data produced during the study from the scheduled study assessments. He ensures the accuracy, completeness, legibility, and timeliness of the data reported to Sponsor in the CRF and in all required reports.

Pre-dose assessments may be performed within 2 hours prior to dosing. The order of priority for pre-dose sampling and assessments are:

1. Vital signs
2. Safety laboratory tests
3. Efficacy laboratory tests

After ILB administration, it is important that sampling for pharmacokinetics (PK) occurs as close as possible to scheduled time. In order to achieve this, the order of priority is:

1. Blood samples for PK and Hepatocyte Growth Factor (HGF). The time points for PK-HGF sampling will start from the start time of IMP injection.
2. Blood samples for Activated Partial Thromboplastin Time (APTT)

## Demographics and other baseline characteristics

### Informed consent

Information about the aims and procedure for the planned investigation, including information on contraception and medication, will be presented to the patient. Signed informed consent must be obtained before any screening procedures are initiated at Visit 1a.

### Demographic information

The following demographic data will be recorded: gender, age, and ethnic origin.

### Weight and height

Height will be measured at screening (Visit 1a) in patients without shoes and reported in centimetres. The body weight will be recorded at Visit 1, 2 and 7, without shoes in light clothing, and be reported in kilograms. Body Mass Index (BMI) will be calculated from the height and weight recorded at Visit 1 and rounded off to the nearest whole number. The body weight recorded at Visit 2 will be used for calculation of the IMP volume to be administered at Visit 2 to Visit 6.

### Medical history

Relevant medical history will be obtained by interview (Visit 1a).

### Prior and concomitant medication

Relevant prior and concomitant will be obtained by interview (Visit 1a).

### HIV and Hepatitis B/C

Patients will be tested for HIV and hepatitis B and C (serum) at the screening (Visit 1a) to verify that eligibility criteria are met.

### Drug screen

Patients will be tested for drugs of abuse at screening (Visit 1a) to verify that eligibility criteria are met. Urine will be tested for opiates, cocaine, cannabinoids, benzodiazepines and amphetamine. Additional random tests can be performed during the study period.

### Alcohol abuse

Patients will be tested for gamma glutamyltransferas at screening (Visit 1a) to evaluate alcohol abuse.

### Pregnancy

Women of child-bearing potential will be tested for pregnancy (urine) at Visit 1a and Visit 2 to Visit 9.

